**Meningitis surveillance and incidence calculations**

Once a HA has been included in the study, a case-based surveillance system will be put in place in health centers, or reinforced if one is currently in place in the study area.

Suspected cases of meningitis that present to health posts will be referred to the nearest health center. In each health center, the diagnosis and treatment of meningitis will follow national protocols.

In line with current international recommendations, the following case definitions will be used:

- Suspect case: Abrupt fever (>38.5°C rectal or >38.0°C axillary) and at least one of the following signs: neck stiffness, floppy neck, bulging fontanelles, convulsions or other meningeal signs.
- Confirmed case: Isolation or identification of a causative organism (*Neisseria meningitidis, Streptococcus pneumoniae, Haemophilus influenzae serotype b*) in the CSF of a suspect case by culture, PCR or agglutination test.

For each suspected case presenting to a health center or district hospital, the following information will be recorded: Age, sex, village of origin, vaccination history, treatment(s) received, presence of sequelae, results of field-based laboratory tests, outcome. A unique identifier will be assigned following the national recommendations for case-based meningitis surveillance. In the setting of the current trial, information about whether the suspected case had received a dose of ciprofloxacin will also be recorded on the standardized forms.

Lumbar puncture and CSF analysis will occur following standard protocols and procedures. Any information collected as a result of this procedure and potential tests will be recorded in the national surveillance system in place. All clinical care will be identical between study arms.

Once the first case has been notified from a village after the study has opened in a health area, a team of community health workers will perform a village census, so as to provide the most accurate possible information for the calculation of meningitis incidence. This census will happen in parallel, or even after, the study interventions described below.

**Target population**

All residents of included villages will be eligible for participation in the study.

For participants in the arms which receive ciprofloxacin, the only persons ineligible to receive ciprofloxacin will be persons currently exhibiting symptoms consistent with meningitis (who will be immediately referred to the nearest health center) and persons with a known allergy to fluoroquinolone antibiotics.

**Study sites**

Study activities will take place in the District Hospital of the Health District in question, as well as in the health centers of HA included in the study. Each health center will have its usual complement of clinical and paraclinical staff necessary during an outbreak. Each health center will also have dedicated study staff whose roles are defined below.

Additional study activities will take place in the villages and in participants’ homes. All distributions of ciprofloxacin, whether household-level or community-wide, will happen in the community. Participants in the resistance sub-study will collect their samples at home and return them to study personnel in their communities. (See below for further detail.)

**Study procedures**

*Interventions*

In the standard care arm, after the first case has been notified from a village, a study nurse will visit the village with a local community member. The study nurse will lead an informational session for members of the community regarding the signs and symptoms of meningitis, and the urgency of presenting to the nearest health center as soon as possible if any of those signs or symptoms arrive.

In the household-level prophylaxis arm, each time a case is reported from a village that has been randomized to this arm, a study nurse will visit the household of the notified case within 24 hours. The study nurse will offer ciprofloxacin to all persons currently living in the same household compound and present at the time of the visit. Household members who have accompanied the notified case will be offered ciprofloxacin at the health center / district hospital. All doses of ciprofloxacin will be directly observed. If a household member is absent during the study nurse visit to the household, a return visit will be arranged.

In this study, a household will be defined as a group of people living in the same building or group of adjacent buildings and under the authority of a single head of household. In the case of polygamy, all wives (and their children) of a male head of household will be considered to members of a single household, provided that they live in the same building or group of adjacent buildings. In the case of multiple heads of household living in one compound of houses, only persons living under the authority of the head of household of the declared meningitis case will be considered a household member and therefore invited to take ciprofloxacin.

In the community-level prophylaxis arm, after the first case is reported from a village that has been randomized to this arm, a member of study staff will visit the village within 24 hours. During this visit, arrangements will be made for a community-wide distribution of ciprofloxacin, preferably within 72 hours of the initial case presentation at the health center / district hospital. These distributions will be organized in collaboration with local administrative and health authorities, such as village chiefs and community health workers, and will take place after a series of community meetings explaining the study and the nature of the distribution to the inhabitants of the village. A sensitization plan will be agreed in each village. All doses of ciprofloxacin will be directly observed.

*Dosing and administration of ciprofloxacin*

Oral ciprofloxacin will be dosed based on age following the guidelines set forth in the table below. Tablets will be administered with water. Children unable to swallow pills will have the tablet crushed and dissolved in sweetened water. The oral suspension will be prepared according to manufacturer’s instructions.

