**METHODOLOGY**

**Overall study design and study launch criteria**

The study is designed as a cluster-randomized trial with three parallel arms in the setting of a meningitis epidemic to assess the impact of chemoprophylaxis with single-dose ciprofloxacin on the incidence of meningitis in the study area.

The study will be implemented in a health district where a meningitis outbreak is occurring, and where Médecins Sans Frontières is providing assistance to the Ministry of Public Health in its outbreak response. In order to launch the study protocol, at least two Health Areas (HA) of the Health District (HD) will have met the weekly meningitis epidemic threshold of 10 cases per 100 000 per week, or of 5 cases per week if the population of the HA is less than 30 000 people, following the most recent WHO recommendations for meningitis surveillance. Other factors (predominant causative serogroup, timing during the meningitis season, plans for reactive vaccination) will then be taken into account before seeking administrative approval in the district in question for the trial to be started.

All villages in the HAs included in the study are will be eligible for inclusion in the study. They will be randomized in a 1:1:1 ratio to receive standard care, household-level prophylaxis, or community-wide prophylaxis. Villages will receive their intervention after the notification of the first case from the village after the study has opened in a HA.

The primary aim of the study is to assess the impact of chemoprophylaxis with ciprofloxacin on the incidence of meningitis, which will be assessed until the end of the epidemic in the study area. Cases of meningitis will be identified using facility-based surveillance.

A nested substudy to describe the effects of ciprofloxacin prophylaxis on the prevalence of ciprofloxacin-resistant enterobacteriaceae will be carried out among 400 persons (200 in the standard care arm and 200 in the community-wide prophylaxis arm). Participants will provide a series of 3 stool samples for culture, speciation, and antibiotic resistance testing.

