In villages selected for the resistance sub-study (in both the standard care arm and community-level prophylaxis arm), participants will be identified at the time of the community sensitization messages being delivered by a study nurse in conjunction with a laboratory technician. A stool sample container will be distributed to each participant, with instructions on how to collect the sample the following morning. Study staff will then return to the village the following morning to collect the fresh stool samples. The same procedures will be followed on days 7 and 28, with one visit to provide the sample container and a second visit to pick up the fresh samples the following morning. Day 0 samples will be collected up until the time of ciprofloxacin administration in the village. At day 7 and 28, samples will also be accepted the day following the scheduled sample collection (i.e., days 8 and 29), if the participant is not able to provide a stool sample on the scheduled day.

*Sample processing*

The processing of stool samples will depend on the location of the study and its distance from the principal study lab in Maradi. The processing of samples will be detailed in the study SOPs. In brief, stool samples will be collected by study staff and either stored at 4°C or inoculated in a transport medium until reception in the central lab. Stool samples will then be plated on a MacConkey agar plate containing ciprofloxacin. After incubation, colonies will be identified using standard microbiological methods. Antibiotic resistance profiles will be determined using the disk diffusion method. The minimum inhibitory concentration (MIC) of relevant antibiotics will be determined. All identified strains will be stored in the Epicentre lab at Maradi. A total of 10% of samples will be sent to a reference laboratory for quality control purposes.

*Participant retention*

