Therefore, in villages randomized to household-level prophylaxis, when the study nurse visits an eligible household, he or she will present the study, its interventions, procedures to be followed and the risks and benefits of participation following the text presented in the informational notice for participants (Appendix B). The members of the household will be given opportunity to ask questions and only those willing to take ciprofloxacin will be administered the drug.

In villages randomized to village-wide prophylaxis, a series of community informational sessions will be organized in advance of the distribution. A text (Appendix B) that presents the study, its interventions, the procedures to be followed, the voluntary nature of participation and the risks and benefits of participation will be read during this meeting, and community members will be given the opportunity to ask questions. The logistical setup of these informational sessions will vary depending on village size and other factors, but the goal will be to have one session for each 25 households, as to allow for better participation. Similarly, during the sensitization campaigns prior to the distribution, the voluntary nature of participation will be underlined. Those people who present to the distribution site will therefore be considered to have been duly informed of the risks and benefits of their taking ciprofloxacin and the voluntary nature of their participation.

The plan outlined in the above two paragraphs is in line with the Ottawa Statement and the criteria set out by Sim.

Written informed consent will be sought prior to inclusion in the resistance substudy. Prior to collection of the first sample, the study nurse will read aloud in the local language the informational notice and informed consent form for the substudy (Appendix C). This informational notice will include information on the purpose of the sub-study, procedures to be followed and the risks and benefits of participation. Study staff will give the participant or their parent/guardian ample opportunity to inquire about details of the study and ask any questions. The notice will be read to the participant in the presence of a literate and impartial witness. The witness will sign and date the consent form to attest the consent process appears to be fair and the participant (or their parent/guardian) voluntarily accepts to participate.

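### The arm procedures script a village-wide symptom and urgent-presentation session for standard care only, although symptom information is elsewhere described as for everyone and cases are counted at health facilities

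*Combined protocol and SAP*

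**What the plan says.** The Study procedures section, repeated in the Study design part of the trial summary, sets out what each arm receives after a village's first notified case.

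- **Standard care.** A nurse goes to the village to "lead an informational session for members of the community regarding the signs and symptoms of meningitis, and the urgency of presenting" quickly at the nearest health center.
- **Household prophylaxis.** At each notified case, "a study nurse will visit the household of the notified case within 24 hours". The Informed consent section adds that in the household "he or she will present the study, its interventions, procedures to be followed and the risks and benefits of participation", using Appendix B. No village-wide session is described.
- **Community prophylaxis.** The distribution follows "a series of community meetings explaining the study and the nature of the distribution to the inhabitants of the village". The protocol adds: "A sensitization plan will be agreed in each village". The symptom content of the meetings and of the plan is not given.

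Three other places bear on intent. The Interventions entry of the trial summary lists community messages on the signs and symptoms of meningitis with no arm restriction. Risk minimization and benefits lists symptom information as a direct benefit of taking part, and Definition of research subject counts all residents of randomized villages as subjects. The Resistance sub-study section, covering the standard-care and community arms, says that "participants will be identified at the time of the community sensitization messages being delivered by a study nurse".

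On the outcome, the Overall study design section states: "Cases of meningitis will be identified using facility-based surveillance". The suspect-case definition is clinical, and the primary analysis compares village incidence by arm after inclusion.

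**The concern.** An illness enters the primary outcome only if the patient reaches a facility. Telling a whole village what to look for and to present urgently can therefore change the count without changing the disease. If that message is given village-wide in one arm and not in another, it becomes part of the contrast being tested. Randomization does not remove a difference introduced after allocation, and the Data analysis section has no step addressing detection. The protocol makes clinical care identical between arms, but that governs what happens once a patient has presented, not whether the patient presents.

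The comparison most exposed is household prophylaxis against standard care, because the household arm is the one with no village-wide contact in its procedures. If the session raises presentation, standard-care incidence rises relative to the household arm, and part of any observed reduction would not be due to ciprofloxacin.

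There is also a plain inconsistency: staff who follow the arm procedures would not deliver in household-arm villages what the summary and the ethics text lead a reader to expect.

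**Working it through.** **1. The passages side by side**

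| Feature | Standard care | Household | Community |
|---|---|---|---|
| Village-wide session in the arm procedures | Yes | None described | Yes, several meetings |
| Symptom and urgent-presentation content | Stated | Not stated | Not stated |
| Sensitization messages mentioned in the sub-study | Yes | Arm not in sub-study | Yes |
| Symptomatic people met at drug visits sent to a health center | Not applicable | Yes | Yes |

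The last row comes from Key Inclusion and Exclusion Criteria and Target population. It acts in the opposite direction to the first two rows.

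**2. The plan's own figure**

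Inputs from Sample size and Table 2: two-sided alpha 5% (sidedness from Data analysis), power 90%, intracluster correlation 0.025, 300 persons per village, attack rate 1% in standard care, 70% reduction (so 0.3%).

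- Design effect = 1 + (300 − 1) × 0.025 = 8.475.
- Persons per arm before clustering = (1.960 + 1.282)² × [0.01 × 0.99 + 0.003 × 0.997] / (0.01 − 0.003)² ≈ 2,764.
- Villages per arm = 2,764 × 8.475 / 300 = 78.09, rounded up to **79**. The pooled-variance form gives 78.20, also 79.

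The stated 79 reproduces. This point disputes no figure in the plan.

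**3. Illustration of unequal detection**

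The documents give no detection rates. Let r be the share of true cases detected in the household arm divided by the share detected in standard care; r is an assumption. With a true reduction of zero:

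- Apparent reduction = 1 − r.
- Effective sample size per arm = 79 × 300 / 8.475 = 2,796.
- z = (0.01 − 0.01r) / √{[0.01 × 0.99 + 0.01r × (1 − 0.01r)] / 2,796}.
- Two-sided rejection rate = Φ(z − 1.96) + Φ(−z − 1.96).

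| r | Apparent reduction | z | Rejection favouring household arm | Two-sided rejection |
|---|---|---|---|---|
| 1.00 | 0% | 0.00 | 2.5% | 5.0% |
| 0.95 | 5% | 0.19 | 3.8% | 5.4% |
| 0.90 | 10% | 0.39 | 5.8% | 6.7% |
| 0.80 | 20% | 0.79 | 12.1% | 12.4% |

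At 177 villages per arm (Table 2, 1% attack rate and 50% reduction), r = 0.80 gives 22.0%. More villages do not dilute this error; they make it easier to declare significant.

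**4. The opposite direction**

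If repeated household visits and referrals raise detection in the household arm, r exceeds 1. At r = 1.25 and 79 villages, a true 70% reduction appears as 1 − 1.25 × 0.30 = 62.5%, and power falls from 90% to 81%.

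**The case against.** The strongest reply is that the sponsor meant the message for every arm. The summary's Interventions entry and the stated benefits carry no arm restriction, and all residents of randomized villages are research subjects. For the community arm, the sub-study text refers to sensitization messages, and the Informed consent section aims for one information session per 25 households, so village-wide contact there may be more intense than in standard care. This largely stands for the community arm. For the household arm it establishes intent but not delivery: no section places a village-wide session there. Appendices A and B are not in the text reviewed, so their content cannot be checked; however, the Informed consent section has Appendix B presented in this arm only to the visited household.

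Second, shared features narrow any gap: free diagnosis, treatment and referral transport, reinforced surveillance, and a census in every included village. This stands as a reason to expect a modest difference, not as evidence of none.

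Third, a reader might infer that detection does differ and that the bias favours household prophylaxis. The documents do not support that. Nurses return to household-arm villages at every case, and referral of symptomatic people at drug visits occurs in the ciprofloxacin arms only, among contacts whose attack rate the background section puts at about 20 times the community's. These routes push the other way. Nothing shows that the two influences cancel, but nothing fixes the sign either.

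Fourth, larger illustrations need extreme assumptions. A rejection rate of 14.3% requires 70% detection against 90%; 80% against 90% gives 7.1%, and 85% against 90% gives 5.5%. An apparent reduction of 5% to 20% is also well below the 50% to 90% effects in Table 2.

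**Conclusion.** The point holds as a conflict in the text that carries a risk to the primary outcome, and it should be fixed. Only standard care has a scripted village-wide symptom and presentation session. The household arm has household contact only, and the symptom content of the community arm's meetings is unstated, while the summary and ethics text imply that everyone receives the information. With facility-based counting, this risks differential ascertainment, mainly in household prophylaxis against standard care.

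The size is unknown. The 5% to 20% apparent reduction and the 5.4% to 12.4% rejection rate rest on assumed detection ratios of 0.95 to 0.80, an inert drug, 79 villages per arm, a 1% attack rate and a normal approximation; they show sensitivity and do not estimate bias. Whether suspect or confirmed cases make up the primary outcome is not stated; a count of suspect cases would be more sensitive to care-seeking.

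It would go too far to conclude that only standard-care villages will hear the message, or that a positive household result must be an artefact. The first ignores the trial-wide statements and the community-arm sensitization; the second assumes a direction that the documents leave open.

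**What to change.** Amend Study procedures, and the matching text in the Study design summary, so that the same scripted village information session, with the same content and timing, is delivered in all three arms after the first notified case. This brings the procedures into line with the Interventions entry and the stated benefits. For the community arm, say how the session relates to the distribution meetings and the sensitization plan.

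Add one case-form field recording whether a case was first identified at a study visit or distribution, and report it descriptively by arm. Time from onset to presentation and the share of cases confirmed, by arm, would also help readers judge ascertainment. Do not repeat the primary comparison without visit-identified cases: they arise through drug visits in the ciprofloxacin arms only, so dropping them would remove cases from one side and inflate apparent benefit.

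The cost is one added session in each household-arm village, where a study nurse already goes, plus a common script and one form field. The sample size does not change. The amendment is needed before launch, because cases that never present cannot be recovered at analysis.

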**Table 1: Age-based dosing of ciprofloxacin**

| Age | Dose (mg) | Formulation |
| --- | --- | --- |
| >12 years | 500 | 1 tablet |
| 5-12 years | 250 | 1 tablet |
| 1-4 years | 125 | ½ tablet (250 mg tablet) |
| 3-11 months | 100 | 2 ml oral suspension (250 mg/5ml) |
| <3 months | 75 | 1.5 ml oral suspension (250 mg/5ml) |

**Standard care for meningitis**

Throughout the study period, the diagnosis and treatment of meningitis in all health centers in study areas will be provided free of cost to any person, regardless of whether they have participated in a distribution of ciprofloxacin. Health center staff will provide physical examinations, lumbar punctures if necessary, and appropriate antibiotic therapy following national protocols. All patients in study areas who need referral from a health center to the district hospital will be transported free of charge.

Participation in the study will in no way affect the eligibility of a village or a HA for reactive vaccination with a polysaccharide or conjugate vaccine.

**Sample size**

The sample size needed to show a difference in the reduction of the meningitis attack rate will be predicated on multiple factors, some of which can be reliably estimated (risk of developing meningitis among household contacts of cases), and others which cannot be reliably estimated, or which will depend on the study area. The overall size of the epidemic (as measured by cumulative incidence) is not reliably predictable. Average household size and average village size also vary significantly by region of Niger.

Table 2 presents different simulations of the number of clusters necessary given specified attack rates and impacts of the ciprofloxacin intervention under the following hypotheses, using the method detailed by Donner and Klar (1996):

- Risk of type 1 error (alpha) of 5%
- Power of 90%
- Inter-cluster correlation coefficient of 0.025
- Average village population of 300 persons

